### 2.10. Interventions

#### 2.10.1. rTMS

All patients undergoing NEURO^®^ will be hospitalized for 2 weeks. The rTMS will be directed at the primary motor cortex of the patient’s healthy cerebral hemisphere at 2400 pulses a day at a low frequency of 1 Hz, as in the conventional NEURO^®^ protocol (Table 2). The rehabilitation physicians affiliated with NEURO^®^-accredited facilities who are in charge of the patient will administer rTMS. The stimulation intensity is set at 90% of the resting motor threshold for the first dorsal interosseous muscle of the non-paralyzed side. This is the lowest intensity that activates motor-evoked potentials in a muscle. A figure-8 coil with a 70 mm diameter and a Mag Pro R 30 stimulator (Mag Venture Company, Farum, Denmark) are used for stimulus irradiation. The duration of treatment with NEURO^®^ and the method of rTMS irradiation are not changed between the control and intervention groups.

#### 2.10.2. Rehabilitation

Rehabilitation, as in the previous NEURO^®^ protocols, will consist of up to six 20 min intervention sessions per day for all patients, except on Sundays and the days of admission and discharge. Rehabilitation in NEURO^®^ is delivered according to prescribed methods by therapists who practice NEURO^®^ at certified medical institutions. Occupational therapy will be provided for a minimum of three sessions per day. The assignment of occupational therapy and physical therapy sessions will be determined by the attending physician with the patient’s consent, considering the patient’s needs, goals, and physical function. Moreover, all patients will be required to perform 60 min of independent training twice a day [4,5,6]. The method of assigning occupational and physical therapy sessions will be kept consistent between the control and intervention groups. In this study, the goals of occupational therapy and the content of the exercises provided in the intervention group will be defined.

### 2.11. Intervention for the Control Group

The control group will receive occupational therapy as per conventional NEURO^®^ [4,5,6]. Functional exercises, such as proximal and distal upper extremity joint movements, muscle mobilization, movement exercises including reaching and manipulation of objects, and daily living exercises to promote the patient’s goals and use in daily life will be performed. The patient will be encouraged to use the paralyzed side of the body for self-training and to manage daily life situations.

### 2.12. Treatment for the Intervention Group

In the intervention group, (1) the difficulty level of practice will be set according to the severity of motor paralysis, (2) the amount of practice necessary for the recovery of motor paralysis will be set, and (3) the treatment goals of the patient and therapist will be set with regard to the functional practice performed in occupational therapy. Movement practice including reaching and manipulation of objects and daily living practice to promote the patient’s goals and use in daily life will be performed using the same intervention methods as in conventional occupational therapy [4,5,6].

The exercise difficulty level will be selected from four plans, according to the scores of shoulder flexion to 90° during elbow extension in Part A and finger extension in Part C of FMA-UE (Figure 2). In studies investigating the hierarchy of difficulty levels of FMA-UE, the synergic movement difficulty level was lower than the difficulty level in shoulder flexion to 90° during elbow extension [27,28,29]. The ability or inability to perform shoulder flexion to 90° during elbow extension is considered a criterion to determine whether a patient is able to perform movements other than the synergic movement (Figure 3). Shoulder flexion to 90° during elbow extension and finger extension reportedly play a role in the functional prognosis of motor paralysis [30,31,32]. In the case of ADL, reaching movements to the target body part or object are planned, followed by skillful finger movements. Therefore, the patient’s ability to perform shoulder flexion to 90° during elbow extension is considered an indicator of whether the practice of the proximal or distal part of the upper limb should be prioritized. Each plan is assigned a menu of exercises with reference to studies that have examined the hierarchy of difficulty levels in the sub-items of FMA-UE [27,28,29]. Each plan includes five exercises for one-to-one practice with the occupational therapist and self-training for the patient (Table 3). We will introduce one of the five functional exercises after a discussion between the patient and therapist and after obtaining the patient’s agreement on the exercises that are highly relevant to their daily activities and those that are requested by the patient. Different training menus may be set for one-to-one training and self-training. However, they cannot be changed during the hospitalization period or mid-session. The exercises can be divided into the following three types, depending on the amount of assistance required and load of the exercise: (1) exercises to move the paralyzed limb with resistance (active resistive exercises), (2) exercises to move the paralyzed limb without resistance or assistance (active free exercises), and (3) exercises to move the paralyzed limb with manual guidance from the therapist or with assistance from the patient’s non-paralyzed limb (active assistive exercises). The exercises are categorized based on whether the joints are moved by the therapist or external forces (passive exercise) [33,34]. In the present study, exercises including voluntary movements are assigned under four plans. Passive exercises, such as stretching to decrease muscle tension and joint exercises to increase range of motion are not included in these four plans. Passive exercises are to be performed by the therapist while conditioning the patient’s body prior to the functional exercises or when relaxing between treatments, as appropriate.

The patient’s posture during practice and the load of the exercise are determined according to the patient’s physical function, such as motor paralysis, muscle tone and balance, and the purpose of the exercise to be performed. The occupational therapist is not allowed to change the content of the set joint exercises but is allowed to change the posture and the amount of load during the exercises according to changes in the patient’s muscle tone, muscle output, and motor paralysis. Figure 4 shows the method for determining the posture, and Figure 5 shows the method for determining the practice load.

The upper-extremity movements will be performed 100 times each per day for a total of 500 times, from a menu of five exercises. These exercises should be performed on a one-to-one basis between the occupational therapist and the patient. The number of upper-extremity movements in self-training will not be included in the number of five exercises. The patient is expected to perform a total of 500 joint exercises per day, including occupational therapy for functional exercises, except on Sundays, the day of admission, and the day of discharge. For example, when a patient is admitted on Monday and discharged on the following Saturday, they will perform a minimum of 5000 joint movements for functional exercises (Table 2).

We estimate that patients will perform more than 5000 upper-extremity movements during their hospitalization because, in addition to regular training, functional exercises, object handling practices, and ADL training will be scheduled. Peurala et al. reported that during a two-week period of hospitalization in which constraint-induced movement therapy was performed, a practice period of 20–56 h was effective in improving upper limb function [20]. Han et al. simulated the number of reaching movements to increase voluntary use of the paralyzed upper limb and reported that 420 movements per session were the threshold [19]. All patients undergoing NEURO^®^ will receive two hours of therapist-led rehabilitation and two hours of patient-led training per day, except on the day of admission, the day of discharge, and Sundays, during a two-week inpatient treatment period.

The minimum number of functional exercises in the intervention group will be 500 per day. The protocol of the intervention group meets the requirements of the amount and duration of exercises reported in previous studies. This study is planned in 14 NEURO^®^-certified facilities in Japan: The Jikei University Hospital, The Jikei University Daisan Hospital, Tokyo General Hospital, Nishi-Hiroshima Rehabilitation Hospital, Kimura Hospital, Kyoto Ohara Memorial Hospital, Izumi Memorial Hospital, Hakodate Shintoshi Hospital, Aomori Shintoshi Hospital, Hattanmaru Rehabilitation Hospital, Atsuchi Rehabilitation Hospital, Ainomiyako Neurosurgery Hospital, Shinagawa Rehabilitation Hospital, and International University of Health and Welfare Ichikawa Hospital. A total of 15 professionals with at least five years of experience in NEURO^®^ rehabilitation were selected as therapists. The level of difficulty of functional exercises in the occupational therapy intervention used in this study was discussed with them and decided upon via consensus. In the past, the treatment and evaluation of patients undergoing NEURO^®^ have been performed by occupational therapists who have completed the prescribed training at NEURO^®^-accredited facilities. The treatment and evaluation procedures for the intervention group will be fully explained to the occupational therapists by at least one expert selected at each site who has discussed this study protocol with the occupational therapists. The expert at each site will supervise the occupational therapists to ensure that they fully understand and implement the study protocol for the intervention group.

The treatment goal is set according to the study by Hamaguchi et al. [23], and the predicted value of recovery of upper limb motor function by NEURO^®^ is calculated using the FMA-UE score obtained on the first day of hospitalization [23]. The physician-in-charge will explain to the patients the predicted score at discharge, the target ADL, and the plan of functional exercises to be performed to achieve the goal. They also promote the patient’s understanding of these plans. These procedures are performed by the physician and occupational therapist within two days of admission.

### 2.13. Outcome Evaluation

The outcomes will be evaluated primarily by FMA-UE. FMA-UE is a comprehensive battery of tests that examines motor function, balance, range of motion of the joints, and degree of joint pain in stroke patients [35]. The motor function items of the upper limb are scored on a 66-point scale using a 3-point ordinal scale. Joint and isolated movements are evaluated in accordance with the recovery stage of motor paralysis. The total score of FMA-UE is classified into no (<23), poor (≤23–≤31), limited (≤32–≤47), notable (≤48–≤52), and full (≤53–≤66) capacities using the severity reported by Hoonhorst et al. [36].

The secondary assessment is an Action Research Arm Test (ARAT). ARAT is an upper extremity functional assessment tool based on the upper extremity test [37,38]. It consists of four sub-items and includes tasks of grasping and carrying objects, manipulation, and reaching to one’s own body. It is scored on a 57-point scale using a 4-point ordinal scale. As a second secondary evaluation, the Wolf Motor Function Test (WMFT) will be used. The WMFT consists of six tasks involving upper-extremity movements and nine tasks of object manipulation [39]. In the WMFT, the performance time of each task is measured, and the quality of movement is scored using a 6-level ordinal scale. In addition, the Jikei Assessment Scale for Motor Impairment in Daily Living (JASMID) will be used to examine the use of the affected upper limb in daily life [40]. JASMID is a patient-reported outcome that was developed based on Motor Activity Log and adapted to the Japanese lifestyle [41,42] and has been used in a previous NEURO^®^ study [23]. JASMID consists of 20 questions related to upper limb movement and evaluates the frequency of use and quality of movement of the upper limb on the affected side on a 5-point ordinal scale. The FMA-UE and ARAT will be used to measure the therapeutic effects of mild motor paralysis, which may be underestimated due to the ceiling effect. For patients with mild symptoms, the WMFT and JASMID will be used to evaluate the treatment effect using the task performance time, frequency of use of the upper extremity on the affected side, and quality of movement [43,44]. Since sleep duration influences the promotion of neuroplasticity in the brain, we investigate patients’ sleep duration and sleep quality using a questionnaire [45]. Patients are asked to respond to the sleep quality questions using a 3-point scale (1: did not sleep well, 2: unsure, 3: slept well).

### 2.14. Statistical Analysis

A multivariate ANCOVA will be conducted to test the hypothesis that the occupational therapy intervention in this study will improve motor function in chronic stroke patients undergoing NEURO^®^ when compared with conventional occupational therapy interventions. The dependent variable will be the date or period of assessment, and the independent variables will be the change in scores of the primary assessment (FMA-UE) and the secondary assessments (ARAT and JASMID). The covariates are age, sex, BMI, and time since onset. JAMOVI version 2.2.1 (JAMOVI Project, Sydney, Australia) will be used for statistical analysis.

The primary analysis will be conducted when the intervention and control group samples reach a total of 64 cases each in all settings. The secondary analysis will be conducted when the number of patients in each group exceeds 60% of all participating centers (Figure 6).

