Occupational therapists intervene with the aim of helping patients acquire their target movements. They induce neuroplasticity by rTMS after considering the severity of motor paralysis. In previous studies on NEURO^®^, occupational therapy exercises were determined by the physician and therapist-in-charge with the consent of the patient, and 40 to 60 min of treatment were provided twice a day [4,5,6]. However, when compared with the well-established stimulation method of rTMS, the difficulty level, amount of practice, and goal settings in NEURO^®^ are not yet formalized and are dependent on the discretion of the physicians and therapists. Motor paralysis and related disability in daily life are highly individualized; while it is difficult for patients to have an idea of the training and recovery needed, this is not a problem for therapists with sufficient clinical experience. The issues faced include: (1) unclear criteria for selecting upper limb motor exercises based on the severity of motor paralysis, (2) unavailability of guidelines for the number of upper limb exercises to be performed by patients, and (3) unclear goal-sharing between patients and therapists regarding the recovery of upper limb motor function and the use of upper limbs in ADL. Therefore, a formalized occupational therapy in NEURO^®^ will uniformize the treatment method and stabilize the functional recovery of patients.

This study aims to evaluate the therapeutic effect of NEURO^®^ on patients by providing a certain amount of selected functional exercises based on the severity of the patients’ motor paralysis. We also define a research protocol in this study. It is hypothesized that the occupational therapy intervention used in this study will improve the patients’ upper limb motor function compared to the conventional intervention method used for patients who receive NEURO^®^. We believe that if the treatment plan for NEURO^®^ occupational therapy is established according to the characteristics of the patients’ motor paralysis, the patients will be less influenced by the skills and years of experience of the assigned occupational therapist, and the effectiveness of rehabilitation will be more stable than that of conventional occupational therapy. This stability will contribute to the improvement of the patient’s goal for ADL.

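### Section 2.14 misstates the primary model: outcome and predictors are reversed and randomised arm has no role, so the model as written contains no test of intervention against control

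*Protocol article*

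**What the plan says.** The Introduction hypothesises that the study therapy "will improve the patients’ upper limb motor function compared to the conventional intervention method" used in NEURO. Section 2.14 of the Protocol article repeats this as the purpose of the analysis. A multivariate ANCOVA is planned "to test the hypothesis that the occupational therapy intervention in this study will improve motor function", and the comparator is named in the words "when compared with conventional occupational therapy interventions".

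The next two sentences assign every role in that model:

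- Outcome: "The dependent variable will be the date or period of assessment".
- Predictors: the changes in FMA-UE, ARAT and JASMID (the full sentence reads "The dependent variable will be the date or period of assessment, and the independent variables will be the change in scores" of those scales).
- Covariates: "The covariates are age, sex, BMI, and time since onset".

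No other section gives a different model. Section 2.13 makes FMA-UE the primary outcome. The legends of Figure 1 and Table 2 place the assessments on the day of admission and the day of discharge only.

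**The concern.** The hypothesis is a contrast between two randomised arms in motor function. The model that is supposed to test it explains the timing of an assessment by changes in three scales. There are two separate faults. Outcome and predictors have changed places, and the treatment factor is missing.

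At stake is whether the confirmatory analysis is fixed in advance. An analyst cannot obtain a treatment effect from the written model and has to supply the missing term. Several analyses are then open: change by arm, discharge score by arm, arm by time, or one joint test over three scales. Choosing among them once results are visible is the freedom that a prespecified analysis should remove. Masking the group labels (Section 2.9) does not settle which model is primary.

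**Working it through.** **1. The plan's own figure.** Section 2.5 gives α = 0.05, power 0.8, numerator df 1, 4 groups, 4 covariates and a total of 128. It gives no effect size, so 128 cannot be derived from the stated inputs alone. For the ANCOVA F test, the noncentrality is λ = N·f² and the denominator df is N − groups − covariates. With an assumed f = 0.25 (d = 0.5 for two equal arms, since f = d/2):

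- λ = 128 × 0.0625 = 8
- denominator df = 128 − 4 − 4 = 120
- power = 0.8012, and 128 is the smallest N that reaches 0.80

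Over a range of assumed f, the N required is 787 (f = 0.10), 199 (0.20), 128 (0.25), 90 (0.30) and 52 (0.40).

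**2. The roles side by side.**

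| Role | Section 2.14 | Needed for the hypothesis |
|---|---|---|
| Outcome | timing of the assessment | motor function (FMA-UE) |
| Predictor of interest | changes in FMA-UE, ARAT, JASMID | randomised arm |
| Covariates | age, sex, BMI, time since onset | these may stay; none stands in for arm |

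With T for timing and X for the covariates, the written model for patient i is

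T_i = β0 + β1·ΔFMA_i + β2·ΔARAT_i + β3·ΔJASMID_i + γ′X_i + e_i.

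The β terms describe how timing is associated with score changes. No combination of them is a difference between arms.

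**3. Exchanging the sides.** This gives ΔFMA_i = β0 + β1·T_i + γ′X_i + e_i. Two assessments yield 2 − 1 = 1 change score per scale per patient. If T means admission versus discharge, each change score spans both times, so T has no levels to compare. If T means calendar date, β1 is a trend over the recruitment period. Arm is absent in both cases.

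**4. Does the written model respond to treatment?** Illustrative simulation, with these assumptions: 64 per arm, normal outcome with SD 1, four covariates unrelated to outcome, assessment date unrelated to outcome, ordinary regression, two-sided 0.05, 2,000 runs.

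| Model | True difference 0.5 SD | No difference |
|---|---|---|
| Change as outcome, arm as factor | 77.9% reject | 5.5% reject |
| As written (test of the FMA-UE change term) | 4.9% reject | 4.5% reject |

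The Monte Carlo standard error near 5% is √(0.05 × 0.95 / 2000) ≈ 0.5 percentage points, so 4.9% and 4.5% do not differ beyond noise. The result for the written model follows largely from the assumption that date is unrelated to outcome. It illustrates step 2 and is not separate evidence.

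**5. Sample size after correction.** With f = 0.25, N = 128, two groups and the four stated covariates, denominator df = 122 and power = 0.801. Adding admission FMA-UE as a fifth covariate gives df = 121 and power = 0.801. The required N stays at 128.

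**The case against.** The strongest reply is that the intention is plain. The sentence before the faulty one names conventional therapy as the comparator. Section 2.14 triggers the primary analysis when the intervention and control samples reach 64 each. Section 2.9 gives the analyst a dataset in which group is masked. Section 2.5 uses one numerator df, and its 4 groups could mean arm by time, though that is only an inference. A multivariate model named beside three scales suggests that the scores were meant as outcomes. All of this stands, and it makes a drafting or translation slip the likeliest explanation. It does not say which of the several arm comparisons is primary.

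A second reply is that a journal article condenses the full plan. That would excuse a model left unstated. Here the model is stated, and it contradicts the hypothesis in the sentence before it.

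A reader might also go further and infer that the trial would count improvement in both arms as success, since both receive NEURO. On that reading, a pooled pre-post t test on 128 patients with identical arms would be significant with probability 0.920 if the mean change were 0.3 SD of change, and 0.9999 if it were 0.5 SD. The documents do not support this as a consequence of the plan. No section proposes a pooled pre-post test, the mean changes are assumptions, and change scores leave no period to test. The literal model shows no inflated error rate. It simply does not respond to treatment.

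**Conclusion.** The point holds as an error of specification. As written, the primary model reverses outcome and predictors and gives randomised arm no role, so it yields no between-arm estimate or test. Exchanging the two sides does not repair it. This is structural and rests on no numerical assumption; the simulated rejection rates (about 5% with or without an effect, against 77.9% for a model with arm) only illustrate it under the assumptions listed.

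An arm comparison was evidently intended, so the text should be corrected as a probable drafting error. It should not be read as a plan to declare success on improvement common to both arms. Nor does the point show that 128 patients is wrong: that figure is reproduced before and after correction at f = 0.25, which is an assumption because the article states no effect size.

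**What to change.** Replace the sentences in Section 2.14 that name the model and the roles of its variables with:

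> The primary dependent variable is the change in FMA-UE from admission to discharge. The fixed factor is randomised arm (intervention vs control). The covariates are admission FMA-UE, age, sex, BMI and time since onset. The treatment effect is the adjusted between-arm difference with its 95% CI. ARAT and JASMID are analysed in separate secondary models of the same form, each with its own admission score as covariate; these replace the single multivariate ANCOVA.

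This text commits to one form of the outcome. With the admission score as a covariate, analysing the change or the discharge score gives the same estimated arm difference. The text also says openly that the multivariate model is replaced, because FMA-UE is the designated primary outcome and a joint test over three scales does not isolate it. WMFT is listed as a secondary assessment in Section 2.13 but does not appear in the Section 2.14 model; the sponsor should say whether it is to be analysed in the same way.

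The cost is a few sentences, with no new data and no change to the planned N at the assumed f = 0.25. The condition is that the wording is agreed before unblinded data are analysed. Section 2.16 plans the study from December 2022 to August 2024, and the article cannot show whether that condition can still be met. If it cannot, the change should be reported as made after the data were available.

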The goal of patients treated with NEURO^®^ is to reacquire ADL using the paralyzed side. In occupational therapy, compensatory movements using the non-paralyzed side, assistive devices, and assistive technology may be applied to supplement the patient’s motor function to reacquire the target activities [16,17,18]. However, in some cases, improving the motor function of the affected side may increase the possibility of patients acquiring the desired ADL. A hemiplegic patient needs at least 20 h of practice during a two-week hospitalization to recover upper limb motor function [19]. The number of stimulated upper limb movements is estimated to be 420 per session [19,20]. Rehabilitation is also more effective when patients are aware of their goals for the recovery of motor function and achievement of ADL [21,22]. Clinical occupational therapists presumably share the treatment goals with patients based on the physician’s prediction of recovery after treatment and provide selected exercises in appropriate amounts according to the characteristics of individual patients’ motor paralysis. The motor function of patients undergoing NEURO^®^ can be predicted using the Fugl-Meyer assessment of the upper extremity (FMA-UE) score [23]. NEURO^®^ reportedly improves upper limb motor function in patients regardless of the stroke type [24]. The content of rehabilitation provided by the therapist presumably affects the patient’s recovery; however, this has not been verified.

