### 2.5. Sample Size

The sample size was estimated via a priori analysis using G*Power. We selected goodness-of-fit (F test) and analysis of covariance (ANCOVA) (for fixed effects, main effects, and interactions) for finding the sample fitness and size. The other data were set as α = 0.05, 1 − β (power) = 0.8, numerator df = 1, number of groups = 4, and number of covariates = 4. Based on this calculation, the minimum sample size was estimated to be 128 (64 in each group). Since the subjects were hemiplegic patients, the minimum sample size was defined as 128 subjects (64 subjects in each group).

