### 2.6. Randomization

A random number table, created using Microsoft Excel (Microsoft, Redmond, WA, USA), will be used for the allocation of patients into the intervention and control groups. The random number table is created at each hospital and maintained by the allocation manager at each hospital.

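### The primary analysis of FMA-UE change leaves admission FMA-UE out of the covariates, which costs some precision and leaves the estimate exposed to chance baseline imbalance

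*Protocol article*

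**What the plan says.** Section 2.14 of the protocol article plans a multivariate ANCOVA. It states that "the independent variables will be the change in scores of the primary assessment (FMA-UE) and the secondary assessments (ARAT and JASMID"). I read these change scores as the outcomes; the naming of dependent and independent variables is a separate matter. The adjustment set is "The covariates are age, sex, BMI, and time since onset". Section 2.5 was computed with "numerator df = 1, number of groups = 4, and number of covariates = 4", so the count agrees with the four named covariates. The list is therefore a stated choice and not an abbreviation.

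Elsewhere the protocol gives admission FMA-UE a central role. The Introduction says that motor function under this treatment "can be predicted using the Fugl-Meyer assessment of the upper extremity (FMA-UE) score". Section 2.12 calculates each intervention patient's predicted recovery from the first-day score. Section 2.13 expects the effect in mild paralysis to be underestimated because of a ceiling. Section 2.3 sets no FMA-UE range for entry, and Table 1 has a severity class reaching 66. The legend of Figure 1 confirms assessment at admission and at discharge.

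Section 2.7 specifies simple randomisation. On hospitals, Section 2.6 says: "The random number table is created at each hospital and maintained by the allocation manager at each hospital". Hospital is not a model term.

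**The concern.** The baseline value of the outcome is usually the first covariate to enter an ANCOVA, and here it is the one left out. A change score subtracts the baseline with a fixed slope of 1. If patients near the ceiling gain less, or if low admission scores partly regress upwards, change still depends on the starting score. That dependence then stays in the error term, and a chance difference in severity between the arms moves the estimated effect. Simple randomisation does nothing to limit such a difference.

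At stake is a modest amount of power, and the credibility of the result if Table 1 shows the arms starting at different levels. Adding the covariate after seeing such an imbalance would look data-driven.

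**Working it through.** **Inputs from the protocol.** Section 2.5: "α = 0.05, 1 − β (power) = 0.8"; numerator df 1, 4 groups, 4 covariates; total 128, 64 per group. Section 2.12: 14 hospitals.

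**Assumptions, because the protocol gives no figure.** Effect f = 0.25, that is d = 2f = 0.5 SD of change; equal SDs at both visits; admission-discharge correlation r of 0.7 to 0.9; between-hospital intraclass correlation (ICC) of 0 to 0.10.

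**1. Reproducing the stated size.** Noncentral F with λ = f² × N = 0.0625 × 128 = 8 and df2 = 128 − 4 − 4 = 120 gives power 0.801, and 128 is the smallest N that reaches 0.80. The f that gives exactly 0.80 at 128 is 0.2496. So 128 reproduces if f = 0.25.

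**2. Precision lost.** With equal SDs, the correlation of change with baseline is −√((1 − r)/2), so adjustment multiplies the residual variance by 1 − (1 − r)/2 = (1 + r)/2. One more covariate gives df2 = 119.

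| r | Variance ratio | λ = 8/ratio | Power at 128 | N for 0.80 |
|---|---|---|---|---|
| 0.7 | 0.85 | 9.41 | 0.861 | 109 |
| 0.8 | 0.90 | 8.89 | 0.841 | 116 |
| 0.9 | 0.95 | 8.42 | 0.821 | 122 |
| 0.95 (beyond the range) | 0.975 | 8.21 | 0.811 | 125 |

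If admission FMA-UE explained nothing, power would stay at 0.801 and N at 128. Without the equal-SD assumption, the variance ratio is 1 minus the squared correlation of change with baseline. Absolute correlations of 0.1, 0.2, 0.3 and 0.5 give power 0.805, 0.817, 0.837 and 0.900.

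**3. Chance imbalance.** The standard error of the difference in mean admission FMA-UE is √(2/64) = 0.177 SD. The 95% limit is 1.96 × 0.177 = 0.35 SD, and the median absolute difference is 0.6745 × 0.177 = 0.12 SD. The change score removes most of this, and a fraction 1 − r carries over. One SD of change equals √(2(1 − r)) SDs of FMA-UE, so an imbalance δ shifts the effect by δ(1 − r)/√(2(1 − r)) = δ√((1 − r)/2) SD of change.

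- At the 95% limit: 0.346 × 0.387 = 0.13 for r = 0.7, and 0.346 × 0.224 = 0.08 for r = 0.9. That is 27% and 15% of the assumed 0.5.
- At the median: 0.05 and 0.03.

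**4. Hospital.** As a fixed factor, hospital uses 13 df. With df2 = 128 − 4 − 17 = 107, the loss of degrees of freedom alone leaves power at 0.800. Adding admission FMA-UE as well (df2 = 106) also leaves 0.800 if neither explains anything. At ICC 0.05 and 0.10 the hospital factor gives 0.820 and 0.840. These figures treat the arms as balanced within hospital, which simple randomisation does not ensure. On average a fixed factor keeps (128 − 14)/(128 − 1) = 0.898 of the information. Then λ = 8 × 0.898 = 7.18, and power is about 0.757, 0.778 and 0.799 at ICC 0, 0.05 and 0.10. For the single covariate in step 2 the same factor is 126/127 = 0.992, which moves power by about 0.003.

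**The case against.** The strongest reply is that the change score has already done most of the work. Predicting the discharge level from the admission level is largely what subtraction removes, so the Introduction and Section 2.12 do not by themselves show that change depends on baseline. This stands in part. The better support is the ceiling remark in Section 2.13, and the size of the dependence cannot be fixed from the protocol. A ceiling could also compress discharge scores, so equal SDs are only a working assumption.

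Three stronger readings are tempting and are not supported.

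- A reader might infer that a baseline imbalance enters the comparison in full. Under the assumptions above only 30% to 10% of it does, and the 0.35 SD limit is an extreme, not a typical, imbalance.
- A reader might infer that the result would be biased or the sample size wrong. Randomisation keeps the unadjusted comparison valid, and the added covariate would hold or raise power.
- A reader might infer from the hospital-specific tables that the design is stratified and the analysis must follow it. Section 2.7 specifies simple randomisation, so the tables force no balance within a hospital. The case for a hospital term rests only on possible outcome differences between hospitals, for which the protocol gives no figure.

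It can also be said that an unseen analysis plan may settle this. However, the article states a complete list and sizes the trial on the same count, so the choice can be judged as written.

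**Conclusion.** The point holds as an efficiency recommendation. Leaving out admission FMA-UE costs about 5% to 15% of residual variance, or 2 to 6 points of power, and leaves the estimate open to a shift of up to about 0.08 to 0.13 SD of change at the 95% limit of chance imbalance. These sizes rest on equal SDs, a correlation of 0.7 to 0.9 and an effect of 0.5 SD of change, none of which the protocol states. Above 0.9 the gain shrinks further. The omission should be corrected because the variable is already collected and including it costs almost nothing. Hospital is a weaker, secondary matter.

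**What to change.** In Section 2.14, analyse the primary outcome in its own ANCOVA: FMA-UE change on group, with admission FMA-UE, age, sex, BMI and time since onset as covariates. Analyse each secondary outcome in a separate model with its own admission value in place of admission FMA-UE. Separate models are needed because a single multivariate ANCOVA shares one covariate set across all outcomes.

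In Section 2.5, change the number of covariates from 4 to 5. The total stays at 128 under the assumed effect, which should be written out.

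As a secondary suggestion, add hospital to account for possible differences between hospitals. Its cost in degrees of freedom is negligible, but a fixed factor also pays for chance splits within hospitals (step 4 of the working). A random intercept is therefore the safer form, because it costs little when hospitals do not differ. It needs a mixed-model routine.

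The cost is a rewrite of the analysis paragraph and one input in the sample size section, with no new data, visits or patients. The change should be made before anyone sees outcome data by group.
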